**Analyses**
Primary outcome
The odds ratio of premature birth (<28/<32/<37 weeks) will be calculated between the three groups
Secondary outcomes
Threatened premature birth, premature rupture of membranes, mode of delivery, low birth weight, admission to NICU, APGAR score, perinatal mortality
Sub analysis
Will be done for severity of grade, number of biopsies/treatments and size of biopsy and/or LLETZ
Confounders
There will be adjusted for potential confounders, such as gemelli pregnancy, premature birth in history, induction of labor, IVF/ICSI pregnancy, pre-eclampsia, diabetes mellitus, diabetes gravidarum, age, smoking, BMI, immunosuppressive drug use, congenital disorders, ethnicity etc.

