**Background**

Cervical cancer screening has been in place in the Netherlands for several decades. Aim of the screening program is to identify and treat premalignant cervical lesions before they progress to cancer. This has led to a strong reduction in cervical cancer incidence and mortality. However, the downside of this screening is unnecessary referral of many women without any abnormalities or lesions that only have very low risk of progressing to cancer. This downside is even more pronounced in the new screening program where high-risk human papillomavirus (hrHPV) testing has replaced primary cytology testing. Most high-risk cervical lesions but inevitably also many lesions with a lower risk are treated by large loop excision of the transformation zone (LLETZ). Various studies and meta-analyses point to an increased risk of perinatal complications such as preterm delivery, low birth weight, premature rupture of membranes and caesarean delivery after LLETZ treatment. Therefore, overtreatment of fertile women has main priority for policymakers. However, it is unknown whether this increased risk is only due to the excision procedure itself, to the underlying cervical intraepithelial neoplasia (CIN) or to secondary risk factors which are associated with both preterm birth and CIN. The purpose of this study is to investigate the association between untreated CIN, treated CIN and adverse obstetrical and perinatal outcomes.

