**Methods**

To answer the research question we started to explore the possibilities of linking treatment data of CIN from the Dutch pathology database (PALGA) with the Dutch perinatal database (Perined). For this purpose involvement of a trusted third party (ZorgTTP) and Statistics Netherlands (CBS) is considered necessary for linking PALGA data to perinatal outcome data from Perined. A mandatory condition is that personal identifiers of the mother are available and that pseudonyms of PALGA and Perined can be harmonized. Furthermore the procedure must meet all current privacy legislation issues.
A specially designed ‘Privacy Verzend Module’ (PVM) delivered by ZorgTTP will be used to convert ZorgTTP pseudonyms (based on social security number (BSN)) into CBS BSN-pseudonyms and to send them to CBS. At CBS the BSN-pseudonyms will be linked and the corresponding BSN will be assigned. Based on the secondary keys (such as date of birth, postal code and sex) the linking results will be checked. When identical the variable ‘Rinpersoon’ is added to the dataset. Based on ‘Rinpersoon’ the PALGA data are linked to the Perined data (Rinpersoon_mother).
After linkage of the PALGA and Perined data at CBS, the researchers will analyze only anonymized data within the CBS ICT environment.

**PALGA selection**Three groups will be selected in PALGA.

Group 1) Women with untreated CIN
Inclusion criteria:
 - Period: 01-01-2005 until 31-12-2015
 - Age: 29-41 years at date of CIN diagnosis (so women invited for three screening rounds are
 included: age 30, 35 and 40)
 - Histologic diagnosis: CIN1, CIN2, CIN3 or AIS diagnosed via biopsy
 Exclusion criteria: histology through treatment, such as LLETZ, ablation, hysterectomy or other.
Group 2) Women with treated CIN
Inclusion criteria:
 - Period: 01-01-2005 until 31-12-2015
 - Age: 29-41 years at date of CIN diagnosis (so women invited for three screening rounds are
 included: age 30, 35 and 40)
 - Histologic diagnosis: CIN1, CIN2, CIN3 or AIS diagnosed via biopsy or treatment
 - Requirement: at least one treatment outcome through LLETZ
Group 3) Control group: women without CIN
Inclusion criteria:
 - Period: 01-01-2005 until 31-12-2015
 - Cytologic diagnosis: normal cytology
Exclusion criteria:
 - Cytologic diagnosis: ASCUS or more in history or follow-up
 - Histologic diagnosis: CIN1 or more in history or follow-up
Group 3 will be matched (1:3?) with group 1 and 2 based on age at and year of diagnosis and urbanization.

Variables

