**Changes after peer review:**
- We included unadjusted analyses for all outcomes in the supporting information
- We included the data of the dose response relationship between increasing severity of CIN or more aggressive treatment with preterm birth of <32 weeks and <28 weeks, instead of only <37 weeks
- Instead of only dichotomized outcomes for preterm birth, we also included a quantitative measure of prematurity in days/weeks of gestation
- We divided supplementary figure 4 into a four panel graph

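### No grade adjustment is specified for the treated versus untreated CIN odds ratio, so that ratio does not by itself separate the excision from lesion severity

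*Protocol*

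**What the plan says.** The Background names three candidate explanations for the excess preterm risk after LLETZ: the procedure, the underlying CIN, and risk factors shared by both. It then states the aim in terms of association: "The purpose of this study is to investigate the association between untreated CIN, treated CIN and adverse obstetrical and perinatal outcomes".

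On who gets treated, the Background says: "Most high-risk cervical lesions but inevitably also many lesions with a lower risk are treated by large loop excision".

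Under Methods (PALGA selection), the two CIN groups span the same grades but are graded from different material:
- Group 1 (untreated): "Histologic diagnosis: CIN1, CIN2, CIN3 or AIS diagnosed via biopsy".
- Group 2 (treated): "Histologic diagnosis: CIN1, CIN2, CIN3 or AIS diagnosed via biopsy or treatment", with at least one LLETZ outcome required.

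Controls (group 3) are matched to groups 1 and 2 on age, year and urbanization. Histologic diagnosis is among the variables extracted from PALGA.

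Under Analyses, the primary outcome is the odds ratio of premature birth between the three groups. Thirteen confounders are named in an open-ended list, and grade is not among them. Grade is placed under Sub analysis: "Will be done for severity of grade, number of biopsies/treatments and size of biopsy and/or LLETZ". The later change lists mention urbanization as an added covariate and, after peer review, results for "the dose response relationship between increasing severity of CIN or more aggressive treatment with preterm birth" at the earlier gestational cut-offs. Neither mentions grade as a covariate.

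**The concern.** Of the three pairwise contrasts, treated versus untreated CIN bears most directly on the excision. By the protocol's own account, lesion risk influences who is treated. If higher grade, or an exposure that travels with it, also raises preterm risk, the contrast is open to confounding by indication: part of the lesion's risk is credited to LLETZ.

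The stake is larger because the protocol reports that smoking, BMI, sexual behavior and socio-economic status could not be adjusted for. These are plausible members of the shared-risk-factor explanation. Grade is the directly relevant covariate that remains in the data.

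**Working it through.** **Step 1: where grade appears in the protocol.**

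| Place | Role of grade |
|---|---|
| Eligibility, groups 1 and 2 | CIN1 to AIS pooled in both |
| Matching | Not a factor; matching concerns controls only |
| Extracted variables | Collected (histologic diagnosis) |
| Confounder list | Not named |
| Sub analysis | Named |
| Later changes to the model | Not mentioned |

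Nothing in the design balances groups 1 and 2 on grade, and nothing in the specified model adjusts for it.

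**Step 2: could the open confounder list cover grade?** Not readily. Group 3 excludes CIN1 or more, so controls have no grade. Grade cannot enter a three-group model as an ordinary covariate. It needs either a separate group 2 versus group 1 model or grade-by-treatment categories, and the protocol describes neither.

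**Step 3: illustrative size.** The protocol gives no figure to reproduce. All inputs here are assumptions:
- share with CIN3/AIS among treated women, pT = 0.50 to 0.70
- share with CIN3/AIS among untreated women, pU = 0.10 to 0.20
- risk ratio of preterm birth for CIN3/AIS versus lower grade, r = 1.1 to 1.5, the same in both groups
- no effect of excision

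Spurious risk ratio = [1 + pT(r − 1)] / [1 + pU(r − 1)]

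For r > 1 this rises with pT and falls with pU, so the extremes are (0.50, 0.20) and (0.70, 0.10).

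| r | pT 0.50, pU 0.20 | pT 0.70, pU 0.10 |
|---|---|---|
| 1.1 | 1.05/1.02 = 1.03 | 1.07/1.01 = 1.06 |
| 1.2 | 1.10/1.04 = 1.06 | 1.14/1.02 = 1.12 |
| 1.3 | 1.15/1.06 = 1.08 | 1.21/1.03 = 1.17 |
| 1.5 | 1.25/1.10 = 1.14 | 1.35/1.05 = 1.29 |

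**Step 4: cross-check on the odds-ratio scale, with other assumed mixes.** The assumed preterm risk is 5% in low grade, and the assumed lesion odds ratio is 1.2 to 2.0. The entries are the grade-unadjusted treated versus untreated odds ratios.

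| High-grade share, treated vs untreated | True excision OR 1.0 | True excision OR 1.5 |
|---|---|---|
| 50% vs 50% | 1.00 | 1.495-1.50 |
| 70% vs 50% | 1.04-1.14 | 1.55-1.70 |
| 80% vs 30% | 1.09-1.39 | 1.64-2.08 |
| 90% vs 20% | 1.14-1.59 | 1.70-2.38 |

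One entry in full (80% vs 30%, lesion OR 1.5, excision OR 1.0). High-grade odds are 0.05263 × 1.5 = 0.07895, a risk of 0.07317. The treated risk is 0.8 × 0.07317 + 0.2 × 0.05 = 0.06854. The untreated risk is 0.3 × 0.07317 + 0.7 × 0.05 = 0.05695. The odds ratio is 0.07358/0.06039 = 1.22.

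With a lesion odds ratio of 1.0 the true value is recovered whatever the mix. In every scenario the within-grade odds ratio equals the assumed excision effect, which is why stratifying or adjusting resolves this component.

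**The case against.** Several stronger readings are tempting, and the protocol does not support them.

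- **That grade was certainly left out of the main model.** The confounder list is open-ended, and exact covariates are often fixed in an analysis plan that is not shown here. Excised size sits in the same Sub analysis sentence as grade, yet the protocol gives a specific reason why size could not enter the main multivariate model. So a sub-analysis variable was not automatically barred from it. The text supports only that adjustment for grade is not specified.
- **That the main odds ratio is crude.** It is adjusted for other covariates, and the unadjusted analyses are placed in the supporting information. It is grade-unadjusted as specified.
- **That the study cannot separate lesion from excision at all.** Three planned analyses help. Untreated CIN versus controls estimates the lesion association without excision. The before/after-treatment comparison uses births in women who were later treated. The sub analysis by grade could be informative if done within grade by treatment. In addition, women with biopsy-proved CIN before the pregnancy and treatment only afterwards were placed in group 1, which may narrow the grade gap.
- **That the post-review dose-response item treats severity and treatment as one gradient.** It joins them with *or* and mainly records added gestational cut-offs.
- **That separating the causes is the literal purpose.** The purpose sentence concerns associations. Separation is the motivating unknown.

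These points limit the wording but do not remove the gap. Untreated CIN versus controls gives the lesion association at group 1's grade mix, which may be milder than group 2's. The before/after comparison also shifts age and parity, and nulliparity is on the protocol's own list of preterm risk factors. No text says that the grade sub analysis compares treated with untreated women within grade.

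**Conclusion.** The point holds in this form: neither adjustment for nor matching on grade is specified for the group 2 versus group 1 odds ratio. That ratio therefore does not by itself distinguish the excision from lesion severity, and the other planned analyses fill the gap only in part.

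Under the first set of assumptions above, the distortion runs from 1.03 to 1.29 in risk-ratio terms. It depends on two quantities the protocol does not give: the grade imbalance between the groups and the effect of grade on preterm birth. If either is absent there is no material bias. The protocol supports the direction of the imbalance but not its size, since it also says many lower-risk lesions are treated.

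This goes beyond a missing detail, because it affects how the contrast closest to the motivating question can be read.

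**What to change.** 1. Keep the three-group odds ratios as planned.
2. Add a group 2 versus group 1 model, without controls, adjusted for the worst histologic grade before the pregnancy (CIN1, CIN2, CIN3/AIS). Report the treated versus untreated odds ratio within each grade.
3. Because group 1 is graded on biopsy only and group 2 on biopsy or treatment specimen, add a sensitivity analysis restricted to women with a pre-treatment biopsy grade. Using biopsy grade merely where available would not make the measurement alike in both groups.
4. In the dose-response work, estimate the severity gradient among untreated women. Estimate the number or size of excisions among treated women with adjustment for grade. Size will be limited to the subset in which it could be calculated.

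Cost: no new variable, since histologic diagnosis is already extracted. Intervals will be wider where there are few untreated CIN3/AIS pregnancies, and the biopsy-grade sensitivity analysis will lose women graded only on the treatment specimen. Confounding by smoking and the other undocumented factors will remain and should be stated alongside the result.

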
- Age of women during cytology/biopsy/treatment
- Date of cytology/biopsy/treatment
- Number of biopsies/treatments
- Histologic diagnosis
- Macroscopic description to calculate the size/volume of the biopsy/treatment by a datamining
 procedure.
- Type of treatment cannot be further specified

**Perined selection**- Period: 01-01-2010 until 31-12-2018
- Pregnancies between 16-24 weeks could be in the database, but this is not required
- Pregnancies of 24 weeks and more are mandatory in the database

Maternal variables
- Conception (spontaneous or with medical help)
- General history
- Obstetrical history
- Gravidity
- Parity
- Singleton or multiple pregnancy (twins, triplets etc)
- Gestation in days and weeks
- Age of the mother at childbirth (calculation through date of childbirth and age at histology date?)
- Date of childbirth
- Start of delivery (spontaneous, iatrogenic)
- Way of delivery (spontaneous, assisted vaginal delivery, caesarean section)
- Presenting part during delivery
- Problems during current pregnancy

Neonatal variables
- Birth weight in grams
- Apgar score after 5 minutes
- Congenital diseases
- Admission after birth (high care, intensive care, post-ICHC; period of admission in days)
- Perinatal death (gestation, antepartum/durante partu/postpartum)

Risk factors for preterm birth
- Ethnicity
- Smoking
- Immunosuppressive medication
- BMI
- General history: infectious diseases, auto-immune diseases, organ-transplantation, diabetes
 mellitus, epilepsy, psychiatric diseases, thyroid disorders
- Obstetrical history: curettage in history, history of abortion, history of preterm birth
- Short interval between pregnancies
- Conception through IVF/ICSI/egg donation
- Multiple pregnancy (twins, triplets etc)
- Nulliparous women
- Problems during current pregnancy: maternal infection, pre-eclampsia, gestational diabetes,
 placental problems
- Congenital diseases

Date of histology and date of childbirth will be used to make a selection of women who were treated before and after their pregnancy to additionally compare perinatal outcomes before treatment and after treatment.

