**Parties involved**

Radboudumc, Erasmusmc, BBMRI, Perined, PALGA, ZorgTTP, CBS

**Changes in the plan:**During data-preparation
- We decided to exclude all multiple pregnancies (twins, triplets etc)
**-** We decided to include women with only treatment after the pregnancy, but biopsy-proved CIN before the pregnancy in group 1 (untreated CIN)
- We decided to only use the spontaneous births for our analysis
- We could not adjust for all potential confounders, as not all these data was (well) documented in Perined, such as smoking, BMI, immunosuppressive drug use, sexual behavior and socio-economic status
- We could only calculate the size of the excised volume for a select group of women, as the macroscopic description was not always (in three dimensions) identifiable. We could, therefore, not use this variable in the main multivariate analysis.
During data-analysis
- The two selected groups from PALGA were matched with a control group, but after linking this data with Perined and looking per pregnancy instead of per women the groups were not completely equal anymore based on these matching criteria. We therefore decided, for example, to also include ‘urbanization’ in the multivariate analysis.

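### The confounder list mixes pre-exposure covariates with events that follow CIN diagnosis or LLETZ and sets no timing rule, so a preterm birth after exposure can be adjusted for as history in the next pregnancy

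*Protocol*

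**What the plan says.** The primary analysis is defined in the protocol, Analyses: "The odds ratio of premature birth (<28/<32/<37 weeks) will be calculated between the three groups". Adjustment follows in the same section: "There will be adjusted for potential confounders, such as gemelli pregnancy", and the list continues with "premature birth in history, induction of labor, IVF/ICSI pregnancy, pre-eclampsia, diabetes mellitus, diabetes gravidarum", then age, smoking, BMI, immunosuppressive drugs, congenital disorders and ethnicity. The list is open-ended, and no item is dated relative to exposure.

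Four other places bear on timing:

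- Methods, PALGA selection, sets the exposure window: "Period: 01-01-2005 until 31-12-2015".
- Perined selection sets the birth window: "Period: 01-01-2010 until 31-12-2018".
- The risk factors under Perined selection place two of the listed items in the index pregnancy: "Problems during current pregnancy: maternal infection, pre-eclampsia, gestational diabetes".
- Changes in the plan (During data-analysis) shows that the unit of analysis is the pregnancy: "looking per pregnancy instead of per women the groups were not completely equal anymore".

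Changes in the plan also excludes multiple pregnancies, restricts the analysis to spontaneous births, and reports that smoking, BMI, immunosuppressive drug use and socio-economic status could not be adjusted for. Changes after peer review adds unadjusted analyses.

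**The concern.** A confounder has to precede the exposure, or at least not be affected by it. For a pregnancy that follows CIN diagnosis or LLETZ, pre-eclampsia, gestational diabetes and a congenital disorder of that pregnancy all arise later, so they cannot have influenced whether the woman had CIN or was treated.

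Prior preterm birth is the more serious case because its role depends on its date. Before exposure, it is a proper covariate. After exposure, it is an earlier occurrence of the study outcome under the same exposure. Conditioning on it then removes part of any effect carried through the first preterm birth. It also makes exposed and unexposed women with the same history differ in their underlying tendency to deliver early. Either way the estimate moves toward no effect.

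At stake is how to read the adjusted odds ratio. The Background asks whether the excess risk comes from the excision, the underlying CIN or shared risk factors. That calls for control of shared prior factors, kept apart from events that come after exposure.

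**Working it through.** **No figure to reproduce.** The protocol states no event rate, effect size or sample size. All numbers below rest on assumed inputs and show order of magnitude only.

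**Step 1. Can a prior preterm birth fall after exposure?** Exposure runs 2005-2015, births run 2010-2018, and the unit is the pregnancy. A woman with LLETZ in 2009 and births in 2011 and 2014 fits the stated criteria. If the 2011 birth is preterm, it is an outcome in one record and history in the next. Nothing in the text prevents this.

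**Step 2. Second post-exposure births, recurrence taken as wholly causal.** Assumed: preterm risk at the first birth 5% unexposed and 10% exposed; second-birth risk 3.5% for an unexposed woman without a prior preterm birth; direct exposure OR 2; recurrence OR 5.

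- Odds at 3.5%: 0.035/0.965 = 0.0363. Multiplying by 5, 2 and 10 gives risks of 0.1535, 0.0676 and 0.2662.
- Unexposed: 0.95 × 0.035 + 0.05 × 0.1535 = 0.0409.
- Exposed: 0.90 × 0.0676 + 0.10 × 0.2662 = 0.0875.
- OR without the history term: (0.0875/0.9125)/(0.0409/0.9591) = 2.25. With it: 2.00.
- Loss: 1 − ln 2.00/ln 2.25 = 14% of the log OR.

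**Step 3. Same births, recurrence due only to shared frailty.** Simulation of 4 million women with logit-normal frailty (SD 0.8, 1.0, 1.3) and conditional OR 2 in both pregnancies. Unadjusted ORs are 1.93, 1.90 and 1.86. Adjusted for prior preterm birth, they are 1.88, 1.82 and 1.74. The log OR falls by 4%, 7% and 11%.

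**Step 4. Does timing drive the shift?** A separate calculation used exact cell probabilities and a logistic model with and without the history term. Assumed: baseline log-odds −3 (about 5%), treatment OR 1.5 or 2.0, frailty SD 0.5 or 1.0, and SD of the treatment effect across women 0 or 0.7.

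| Share of prior births after treatment | Shift in log OR |
|---|---|
| None | 0 to +0.6% |
| Half | −0.8% to −4.3% |
| All | −1.6% to −10.5% |

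With no prior birth after treatment there is essentially no shift. The attenuation appears only when history follows exposure.

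**Step 5. Pooling.** A first post-exposure birth carries no post-exposure history, so the effect is diluted. Mixing first births (5% v 10%, OR 2.11) with the second births of step 2, and fitting a logistic model with and without the history term:

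| Assumed share of second births | OR without | OR with | Shift in log OR |
|---|---|---|---|
| 10% | 2.12 | 2.10 | −1.2% |
| 20% | 2.13 | 2.10 | −2.4% |
| 30% | 2.15 | 2.09 | −3.6% |
| 50% | 2.17 | 2.07 | −6.3% |

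**Step 6. Index-pregnancy complications.** Assumed: complication baseline 3%, OR 4 on preterm birth, exposure OR 1.5 or 2.0. If exposure does not affect the complication, adjustment shifts the log OR by about +1%, which is non-collapsibility of the odds ratio. If exposure raises the odds of the complication 1.2- to 2-fold, the shift is −0.8% to −12.9%.

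**Step 7. Can history be ordered against exposure?** Childbirth dates are listed for Perined records, which start in 2010; earlier births appear only as undated history. For exposures from 2010 onward this is no obstacle: a birth before 2010 necessarily came first, and later births are dated. For exposures in 2005-2009, a preterm birth before 2010 may lie on either side.

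**The case against.** The case for leaving the plan alone has several parts.

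- **Consequences of exposure.** A reader might infer that pre-eclampsia, diabetes gravidarum, induction and congenital disorders are consequences of CIN or LLETZ. No section says so. The text supports only that they come later, and step 6 shows that adjustment then matters little. They may even stand in partly for BMI, which could not be adjusted for. This stands.
- **Induction.** The restriction to spontaneous births, if it refers to onset of labor, largely removes induction as a covariate. This stands. Whether that restriction is itself selection on a post-exposure event is a separate question.
- **The list is not the final model.** It is open-ended, some items could not be used, and urbanization was added. True, but no recorded change withdraws prior preterm birth, pre-eclampsia, diabetes gravidarum or congenital disorders.
- **Unadjusted results are reported.** They remove all adjustment at once, so they cannot separate control of confounding from over-adjustment.
- **The estimand.** A reader might infer that a total effect of treatment is the stated target. The Research question asks about association, so that target is a reviewer's reading. The timing problem remains under either reading, because one history term plays two roles.
- **Size.** A reader might carry the 14% loss over to the whole study. It applies only to second post-exposure births with recurrence wholly causal. Pooled, the loss is a few percent and unlikely to change a qualitative conclusion.

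**Conclusion.** The point holds in limited form: the set mixes pre- and post-exposure variables without a timing rule, so the adjusted odds ratio may be biased. For prior preterm birth after exposure, every scenario examined points toward the null. The loss is about 1-15% of the log OR in repeat post-exposure births and about 1-6% when second births make up 10-50% of the pooled data. These sizes depend on the assumed risks, recurrence strength and shares; the documents supply none of them.

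For pre-eclampsia, diabetes gravidarum and congenital disorders, the confounder label is wrong by timing. The cost of adjusting is about 1% unless exposure affects them, which the documents do not establish.

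It would go too far to conclude that the adjusted estimate is over-adjusted instead of freed of confounding. The list also contains proper baseline covariates (age, ethnicity, pre-existing diabetes), and preterm history that precedes exposure belongs in the model. This is a should-fix: modest in size and cheap to address.

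**What to change.** 1. State an exposure date for each contrast (first CIN diagnosis or LLETZ; the matched index date in controls). In the primary model, count prior preterm birth only if it preceded that date.
2. Leave pre-eclampsia, diabetes gravidarum and congenital disorders out of the primary model. Drop induction as redundant if the restriction means spontaneous onset.
3. Where prior births cannot be dated, add an analysis limited to each woman's first recorded post-exposure birth, or to exposures from 2010 onward. The second orders history more cleanly: for a 2005-2009 exposure, the first recorded birth may not be the first after exposure.
4. Show the full listed set as a sensitivity model beside the primary one.
5. Give a reason for keeping or dropping IVF/ICSI conception. It also follows exposure in time but may mark earlier subfertility, and this review takes no position on it.

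Cost: revised wording and model re-runs on data already held. Adjusted estimates may be slightly wider or different, some history will stay undatable, the 2010-onward analysis uses fewer women, and a partial proxy for unmeasured BMI may be lost.
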